## Effectiveness evaluation

To test the effect of RTW-PIA, an effectiveness, a health-economic and a qualitative effect evaluation will be performed.

### *Study sample*

Eligible patients in this effectiveness study will meet the following inclusion criteria:aged between 18 and 60 years,employed for ≥ 15 h per week on the primary labour market^1^ according to German law,current sickness absence period of at least 6 weeks, based on self-report,current principal diagnosis of a mental disorder, classified according to the 10th version of the International Statistical classification of Diseases and Related Health Problems (ICD-10) from at least one of the following sections: schizophrenia, schizotypal and delusional disorders (F2); mood (affective) disorders (F3); neurotic, stress-related and somatoform disorders (F4); behavioural syndromes associated with physiological disturbances and physical factors (F5); disorders of adult personality and behaviour (F6), andfulfil all other entrance criteria for receiving treatment within the psychiatric outpatient clinics of psychiatric hospitals according to §118 (2) of Volume V of the Social Insurance Code [69].

Potential patients will not be eligible to participate if they ***a)*** have a current principal diagnosis of a mental disorder, classified according to the 10th version of the ICD-10, from one of the following sections: organic, including symptomatic, mental disorder (F0); mental and behavioural disorders due to psychoactive substance abuse (F1); ***b)*** have an acute and severe somatic disease (e.g. cancer); ***c)*** are currently pregnant; ***d)*** have decided against returning to the labour market; or ***e)*** have already planned and prepared an approved rehabilitation stay.

### *Recruitment procedure*

Patients who currently receive inpatient, day-care, or outpatient treatment in psychiatric clinics or POCs are screened for eligibility by the trained treatment teams of the respective study centres. A flowchart of the recruitment procedure and the study participants’ progress is shown in Fig. 1. Prior to study inclusion, all potentially eligible patients identified for the study will be invited to the one-time enrolment module “Work and Health”, which includes a psychoeducational group session on the following topics: interdependency of health and work, significance of work and its potential positive and negative effects, occupational integration management, and gradual RTW. At the end of the enrolment module, patients are informed about RTW-PIA and asked about their willingness to participate. Patients who give their written informed consent are then invited to the online baseline assessment. After successful completion of the baseline assessment, the patients are randomised to the IG or CG. The recruitment process started in September 2021.

### *Allocation and blinding*

Patients will be randomly assigned to either IG or CG with a 1:1 allocation, using permuted block randomisation with varying sizes stratified by study centre. Before recruitment began, five randomisation lists were prepared via an online randomisation service [72] by an independent researcher, blinded to the study conditions. For adequate allocation concealment, the generated lists were then securely transferred to an independent administrative working group, to which the evaluators, clinical practitioners, and participants never have access during recruitment. The baseline assessment takes place before group allocation to minimise reporting and selection bias. After completion, all participants will be randomised according to their chronological order of survey participation. The respective randomisation date will serve as the participant´s admission to the study. Blinding among study participants and treatment providers will not be possible before, during, or after the study. Due to the questionnaire design with items concerning the individual intervention modules, the evaluators will also not be blinded.

### *Data collection, outcomes and other measures*

The effectiveness and health-economic evaluation constitute the quantitative study part of the RCT. Self-reported quantitative data will be collected through online surveys and will be pseudonymised. Online assessments will take place at baseline (T0) and at 6 months (T1), 12 months (T2), 18 months (T3), and 24 months (T4) after completion date of the baseline assessment. All study participants will be regularly reminded to participate in the online surveys and receive compensation for their study-related efforts (€10 for each completed online survey). The overall study schedule of enrolment, interventions, instrument assessments as well as measurement time assessments is shown in Table 2. The primary outcome will be the achievement of SRTW. In addition, we will measure a range of secondary outcomes (e.g. health-related quality of life, mental functioning) as well as some further variables (e.g. to describe the sample). Since the study is addressed to German-speaking participants, translated questionnaires and/or ones validated for Germany were used in the online surveys. In the online surveys (T1-T4), the number of questions to be filled in depended on the respondent´s work status (meantime unemployed, etc.) and RTW status and situation (RTW event occurred, or not yet). A broad overview of all further measurements applied to the online survey can be found in Additional file 1.

**Table 2 Tab2:**
[figure not shown]
Study schedule of enrolment, interventions, and assessment

*-T1* Prior to study admission, *T0* Baseline, *T1* 6 months, *T2* 12 months, *T3* 18 months, *T4* 24 months after completion of baseline assessment. *AQoL-6D* Assessment of Quality of Life-6 Dimension [75], *BSI-18* Brief Symptom Inventory-18 [81], *COPSOQ* Copenhagen Psychosocial Questionnaire [78], *F-SozU K-6* Perceived Social Support Questionnaire brief form [91], *KUSIV3* Interpersonal Trust Short Scale [88], *NFAS* Norwegian Function Assessment Scale [76], *PHQ-9* Patient-Health Questionnaire-9 [87], *RTW-SE* Return to Work Self-Efficacy Scale [79], *SIBAR* Screening Instrument Work and Occupation [89], *TiC-P* Trimbos and Institute of Medical Technology Assessment Cost Questionnaire for Psychiatry [74], *WAS* Work Ability Score [83], *ZUF-8* Questionnaire for Patient Satisfaction [94]

^1^Only applied if participant did return to work

^2^Only applied once if participant´s first day back at work was more than 12 months ago

^3^Adapted for Module A

^4^Adapted for Module B

^5^Adapted for Module C

^6^Adapted for overall intervention

^*^Number of questions may vary depending on the participant´s response behaviour as well as the RTW-status

^*1^Duration of the intervention depends on the participant´s needs and may therefore vary

### Primary outcome

The primary outcome will be the employees´ achievement of sustainable RTW. We have defined SRTW when employees report less than six weeks in total of contractually agreed working days missed out due to sickness absence (SA) within 12 months after first returning to work. Thus, the measurement of the primary outcome is based on the following two items: **(I)**
*RTW* and **(II)**
*No relapse after RTW*. The self-adapted, single-item questions presented below are partially based on the Trimbos and Institute of Medical Technology Assessment Cost Questionnaire for Psychiatry (TiC-P) [73, 74].

#### (I) RTW

At T1, T2, T3 and T4, all employees will receive the following self-developed question: “*Have you meanwhile returned to work*?” with the answer options ‘*yes*’ and ‘*no*’. Meanwhile refers to the period since the last completed survey. The selected answer (yes) confirms the employee´s first RTW. The returned employees will be asked to enter their RTW date numerically (“*When was your first day back at work?*” (DD.MM.YYYY)).

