## Background

Mental disorders (MDs) are highly prevalent worldwide [1, 2] and account for a large and increasing part of workforce sickness absence (SA) and disability in Europe [3]. It is estimated that 16% of the total global disability-adjusted life-years could be attributable to MDs [4], resulting in large economic costs to those affected, their employers and society at large [5, 6]. In Europe alone, the economic impact of MDs is predicted to make up more than 4% of its gross domestic product, equivalent to over €600 billion per year [7]. With average SA durations lasting more than twice as long as for all other diseases, MDs are known to be the second most common cause for SA in Germany, where the current study takes place [8]. Between 2000 and 2020, the proportion of mental health-related disability benefits has steadily and significantly increased in Germany, namely from 24.2% to 41.5% [9]. These figures are deeply concerning and call for greater prioritisation and investment for global mental health [10].

To facilitate the recovery process and prevent long-term negative consequences such as unemployment or disability pension [11–13], the return to work (RTW) of individuals with MDs is key [3, 14]. This is a complex process taking place at the intersection of the mental health care system and the workplace, in which the priorities of multiple involved stakeholders are not always aligned [15–17]. However, being back at work carries no guarantee of sustainable reintegration [18], given that most MDs are likely to relapse or recur easily [19, 20]. High rates of recurrent SA or multiple RTW attempts are commonly reported after an episode of mental health-related absence [21–23]. This underlines the necessity for designing both the overall treatment phase and RTW process as sustainably as possible in order to prevent relapses among employees with MDs and to minimise substantial future economic costs for society as a whole.

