#### (II) No relapse after RTW

Those employees who self-confirmed their RTW for the first time at either T1, T2, T3 or T4 (see (I)) will receive the following question: “*Did you stay home sick or call in sick for more than 6 weeks in total after your RTW?*” with the answer options ‘*yes*’ and ‘*no*’. The selected answer ‘*no*’ indicates that employees did not relapse after their RTW and might achieve SRTW in the future. Employees who self-confirmed their RTW to be more than 12 months ago at T2, T3, or T4 with “*My first day back at work was more than 12 months ago”* will receive the following question: “*In the first 12 months after your return to work, did you stay home sick or call in sick for more than 6 weeks in total?*” with the answer options ‘*yes*’ and ‘*no*’*.*

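### The return-to-work items do not tie the 12-month relapse window to the first return, so a participant with two returns can be scored on the wrong one

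*Protocol article*

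**What the plan says.** **Definition.** In the protocol article, Primary outcome, the definition of SRTW reads, up to its last word: "less than six weeks in total of contractually agreed working days missed out due to sickness absence (SA) within 12 months after first returning to". The same section says that the measurement rests on two items.

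**Item I, section (I) RTW.** The item is sent widely: "At T1, T2, T3 and T4, all employees will receive the following self-developed question". Its reference period and the meaning of a positive answer are given together: "Meanwhile refers to the period since the last completed survey. The selected answer (yes) confirms the employee´s first RTW". So the item covers only the latest interval, yet a positive answer is read as a first return. Those who have returned are then asked "When was your first day back at work" and enter a date.

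**Item II, section (II) No relapse after RTW.** An initial relapse question goes to participants who are reporting a return for the first time. A second question goes to those who declare that their first day back lies more than 12 months in the past. It reads, apart from its last word: "In the first 12 months after your return to work, did you stay home sick or call in sick for more than 6 weeks in".

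**Related text.** Data collection, outcomes and other measures says that the questions shown depend on whether the return has occurred yet. Footnote 2 of Table 2 restricts an item to a single use, once the first day back is more than 12 months ago. The Background states: "High rates of recurrent SA or multiple RTW attempts are commonly reported after an episode of mental health-related absence".

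**The concern.** The primary endpoint exists to separate a return that lasts from one that does not. The participants for whom the items are ambiguous are those who came back, fell ill again and came back a second time. The Background describes this as a common course in this population.

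A question about the period since the last survey, put to everyone, will truthfully be answered yes by a first-time returner and by a second-time returner. Calling every such answer a first return does not make it one. If the 12-month question is then answered about the later return, the window that decides the endpoint is not the one in the definition.

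If this happens equally in both arms and mainly turns failures into successes, it shrinks the difference between arms. If RTW-PIA, which accompanies the return process, changes how often people make repeat attempts, it could also bias the comparison.

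**Working it through.** **1. The sections side by side**

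- Primary outcome: the clock starts at the first return.
- (I) RTW: all employees, every survey, latest interval only, yes means first return. For anyone with two returns these statements cannot all hold.
- (II), initial relapse question: limited to first-time reporters. Someone who reported a return at T1 without relapse is not described as getting it again, so a later relapse is caught only by the 12-month question.
- (II), 12-month question: refers to the participant's return without saying which one, and shows no date in the wording given. It is opened by the participant's own statement of elapsed time, not by the stored date.

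**2. Failure scored as success.** Surveys fall at months 6, 12, 18 and 24. Suppose a return at month 2, about 12 weeks off sick in months 7–9, and a second return at month 10.

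- T1 (month 6): yes, date in month 2, no relapse.
- T2 (month 12): yes is again true for the interval since T1, and a month-10 date can be entered. The initial relapse question is not shown, because this is not a first report.
- T3 (month 18): if she thinks of month 2, then 18 − 2 = 16 months have passed. The 12-month question opens and she is correctly scored a failure. If she thinks of month 10, then 18 − 10 = 8 months have passed and it does not open.
- T4 (month 24): thinking of month 10, 24 − 10 = 14 months have passed. The question opens, is asked once as footnote 2 requires, and is answered for months 10–22. She reports no long absence and scores SRTW.

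Under the definition the window is months 2–14. It contains about 12 weeks of absence, so she failed.

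**3. Success scored as failure.** Suppose a return at month 2, 4 weeks off in month 9, back at month 10, then 8 weeks off in months 16–17. Months 2–14 contain 4 weeks, so the definition is met. Months 10–22 contain 8 weeks, so an answer about the second return scores a failure.

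**4. Size, as an illustration.** Inputs from Sample size and power calculation: 60% against 75%, power 80%, significance level 5%, 152 per arm. Sidedness is not stated; a two-sided test reproduces the figure. With pooled variance and no continuity correction:

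n = [1.960·√(2·0.675·0.325) + 0.842·√(0.60·0.40 + 0.75·0.25)]² / 0.15² = (1.298 + 0.550)² / 0.0225 ≈ 151.9, so 152 per arm.

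Let m be the share of true failures recorded as successes, equal in both arms. Each rate p becomes p + m(1 − p), and the difference becomes (1 − m) × 15 points.

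| m (assumed) | CAU | RTW-PIA | Difference (points) | Power at 152 per arm |
|---|---|---|---|---|
| 0% | 60.0% | 75.0% | 15.0 | 80% |
| 5% | 62.0% | 76.25% | 14.25 | 77% |
| 10% | 64.0% | 77.5% | 13.5 | 74% |
| 20% | 68.0% | 80.0% | 12.0 | 67% |
| 30% | 72.0% | 82.5% | 10.5 | 59% |

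The document gives no value for m. Two facts limit it. People who never return, or who relapse and stay off, cannot be recoded by this route. And for the 12-month question to open on a second return by T4, that return must come before about month 24 − 12 = 12. Only relatively early relapsers qualify.

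**The case against.** The strongest reply is that the article plainly means one clock. The endpoint is anchored on the first return, the initial relapse question is filtered to first reports, the 12-month route speaks of the first day back, footnote 2 allows a single use, and the survey adapts to whether a return has occurred. The earlier date would already be on file. In the example, a participant who keeps month 2 in mind is scored correctly at T3. The survey details in Additional file 1 and the analysis plan are not shown, and a rule to use the earliest date is something such a plan commonly holds.

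Most of this stands. A reader might infer that every yes restarts the 12-month clock by rule. The documents do not support that: no section says that a later answer replaces an earlier date. A reader might also infer that the error runs only from failure to success. Step 3 of the working shows that it can go the other way.

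What the reply does not remove is the gap in what is collected. The stated trigger for the deciding question is the participant's own statement, and its wording leaves the choice of return to her. An analysis rule can select the earliest recorded date. It cannot change which return she had in mind when she answered, nor recover a failed first attempt between two surveys that was never dated. The participants' absence lists mentioned in the Discussion are described as a recall aid, and the endpoint is said to rest on the two items.

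**Conclusion.** The point holds as an unguarded risk of misclassification in the primary endpoint, caused by wording under (I) RTW that conflicts with the definition and by a 12-month question that is not tied to a date. It is not a stated rule that resets the clock.

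The size is unknown. The power figures rest on an assumed share of misclassified failures, equal in both arms and in one direction only. At 10%, power would be about 74% instead of about 80%. The stated sample size reproduces and is unaffected.

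The point deserves action because repeat attempts are, by the article's own account, common here, and because separating them from lasting returns is the purpose of the endpoint.

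**What to change.** Reconcile (I) RTW with the Primary outcome definition, the filter under (II) and the routing described under Data collection:

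- Ask for the earliest day worked since baseline, even if the person is now off sick again.
- Put item I, as a first-return question, only to participants with no return yet recorded. Record later returns in a separate item.
- Route the relapse questions on the stored first-return date and show it in each of them (in the 12 months from [date]).

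For surveys already completed, derive SRTW from the earliest reported return date. Count as failure only absence that breaches the defined limit within 12 months of that date, using later return dates and, where available, the participants' absence lists. The 12-month restriction matters: a rule that failed anyone with a long absence before a later return would wrongly fail people who relapsed only after their window had closed.

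The cost is a change of wording and routing during the trial plus one derivation rule, with no extra visits. Completed surveys can be repaired only in part.

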#### (II) No relapse after RTW

Those employees who self-confirmed their RTW for the first time at either T1, T2, T3 or T4 (see (I)) will receive the following question: “*Did you stay home sick or call in sick for more than 6 weeks in total after your RTW?*” with the answer options ‘*yes*’ and ‘*no*’. The selected answer ‘*no*’ indicates that employees did not relapse after their RTW and might achieve SRTW in the future. Employees who self-confirmed their RTW to be more than 12 months ago at T2, T3, or T4 with “*My first day back at work was more than 12 months ago”* will receive the following question: “*In the first 12 months after your return to work, did you stay home sick or call in sick for more than 6 weeks in total?*” with the answer options ‘*yes*’ and ‘*no*’*.*

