The present study has some important strengths. Applying a randomised controlled study design will be the most appropriate method when evaluating the (cost-)effectiveness of RTW-PIA on the employees´ achievement of SRTW. We will include patients with a wide range of MDs to reflect the contemporary clinical practice in Germany. The present study will make an important contribution to the international research field of RTW by implementing an observation period of two years, enabling to examine long-term effects such as the sustainability of the employees´ RTW. By collecting and combining a considerable amount of outcome data on the (cost-)effectiveness and implementation process from several stakeholder perspectives, this multimethodological evaluation design will capture various facets of RTW-PIA in practice and will add to the evidence base for the optimisation of SRTW practices. In addition to publishing our results in international research journals, a revised RTW-PIA manual will be provided for practical use as well as the amended web-based aftercare, which is closely linked to the manual content-wise. Finally, the generalisability of our results across Germany will be supported by the participation of different POCs with both urban and rural contexts, distributed over four German federal states.

Despite this extensive evaluation design, this study faces some methodological limitations. Since there is no central register-based data available on the employees’ SA in Germany, we have to deal with self-assessed data. To minimise possible recall bias, participants will be asked to record the days of SA consecutively in a list provided by the study centres. In addition, the study participants and treatment providers cannot be blinded to the group allocation due to the psychosocial nature of the RTW-PIA modules. Therefore, the risks of both performance bias and subject expectancy bias are difficult to prevent and will be considered when interpreting the final results. Due to the COVID-19 crisis and its aftermath, we expect some challenges with regard to the recruitment of study participants and implementation of RTW-PIA within the clinical setting of POCs due to lower occupancy rates of the clinics, staffing shortages and hygiene measures. However, any possible deviations from the protocol with regard to the recruitment or delivery of RTW-PIA will be continuously documented and considered in the final evaluation.

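### As written, no relapse item is described between first confirmed return to work and the single 12-month question, so a known failure can become a missing value

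*Protocol article*

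**What the plan says.** Under Primary outcome, sustainable RTW (SRTW) means staying below six weeks of contracted working days "missed out due to sickness absence (SA) within 12 months after first returning to work". The subsection on relapse after RTW gives two yes/no items.

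- The first asks whether absence since RTW has exceeded six weeks in total. Its recipients are "Those employees who self-confirmed their RTW for the first time at either T1, T2, T3 or T4".
- The second asks the same about the first 12 months after RTW. Its recipients are "Employees who self-confirmed their RTW to be more than 12 months ago at T2, T3, or T4".

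Surveys fall at baseline (T0) and at 6, 12, 18 and 24 months (T1 to T4). Participants enter with a "current sickness absence period of at least 6 weeks, based on self-report", so first RTW falls after T0.

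The Table 2 grid is not shown. One of its footnotes reads "Only applied once if participant´s first day back at work was more than 12 months ago" and another "Only applied if participant did return to work"; which items they mark cannot be seen. The Discussion adds, as a measure against recall bias, that "participants will be asked to record the days of SA consecutively in a list provided by the study centres".

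Under Statistical analyses, missing primary outcomes are assumed missing at random and handled by chained-equations imputation. Baseline variables that predict missingness are added.

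**The concern.** Once absence within the window has exceeded the limit, SRTW has failed and nothing later can reverse it. A participant who answers a survey after that point could report the failure there and then. If no relapse item is asked at that survey and the person then leaves the study, the failure is never recorded and the outcome has to be imputed.

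The stated imputation strategy draws its predictors of missingness from baseline. A relapse after baseline that itself leads to drop-out is not among them, so the missing-at-random assumption is least safe for these people. The protocol plans for 40% drop-out. An analysis plan cannot restore an answer that was never requested, so this belongs to data collection.

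**Working it through.** **The plan's own figure.** Inputs from Sample size and power calculation: 60% versus 75%, power 80%, significance level 5% (taken as two-sided), 1:1. With pooled variance and no continuity correction:

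n per arm = [1.96 × √(2 × 0.675 × 0.325) + 0.8416 × √(0.60 × 0.40 + 0.75 × 0.25)]² / 0.15² = (1.298 + 0.550)² / 0.0225 ≈ 152.

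For 40% drop-out, 2 × 152 / 0.6 = 506.7, stated as 506. Both figures reproduce, and this point does not change them.

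**Timeline.** Let r be the month of first RTW after T0, with surveys on time.

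| r (months) | First item | Later survey with no described relapse item | 12-month item | Months from RTW to 12-month item |
|---|---|---|---|---|
| 0-6 | T1 | T2 | T3 | 18 − r, so 12 to 18 |
| 6-12 | T2 | T3 | T4 | 24 − r, so 12 to 18 |
| 12-18 | T3 | T4 | not reached | - |
| 18-24 | T4 | none | not reached | - |

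In the first two rows, the 12-month window closed 0 to 6 months before the deciding answer. The part of the window lying after the first item is r + 12 − 6 for r in 0-6 and r + 12 − 12 for r in 6-12. Both give 6 to 12 months, so at least half of the window follows the first item.

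**Example.** A participant returns at month 2, answers no at T1, is off sick from month 6.5 to month 8.5 (2 × 52/12 ≈ 8.7 weeks), completes T2 and leaves before T3. At T2, RTW has already been confirmed and lies 10 months back, so neither item applies as described. The failure is final by month 8.5 but ends as a missing value.

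**People exposed.** The protocol gives no figure, so two assumptions are needed. Drop-out is monotone and even over the four intervals, and 70-80% have first RTW confirmed at T1 or T2, with the same share among those who leave.

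- Drop-out per interval: 40% / 4 = 10% of randomised, and 506 × 0.10 = 50.6.
- The exposed are those confirmed at T1 who leave between T2 and T3, plus those confirmed at T2 who leave between T3 and T4.
- Count: 50.6 × 0.70 = 35.4 to 50.6 × 0.80 = 40.5, or about 35 to 40 people.

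**From exposed to failures.** The planned failure proportions are 1 − 0.75 = 25% and 1 − 0.60 = 40%. Applied to this group they give 35 × 0.25 ≈ 9 to 40 × 0.40 = 16. This is a rough guide only. The planned proportions include people who never return, and some relapses are caught by the first item or occur after the interim survey; both lower the number. Relapse that prompts drop-out would raise it.

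**The case against.** The strongest reply is that the item-by-survey grid is not available. That the first item is asked only once is the natural reading of the relapse subsection, but it is not certain. Only the footnote on RTW more than 12 months ago carries a limit to one occasion, while the footnote conditional on RTW carries none. This stands as a caveat. If the first item is in fact repeated, the subsection needs rewording rather than a new routing.

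Several stronger readings are tempting, and the protocol does not support them.

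- *Relapses in general go unrecorded.* They do not. The first item catches those before first confirmation, and the 12-month item looks back over the whole window for anyone back by about month 12 who stays in the study. If the cost questionnaire is given at each survey, its 3-month recall would also reach part of each interval, although it is not named as a source for SRTW.
- *Success rests on unaided memory.* Participants are to keep a running absence list. The protocol does not say that the list is collected or used to derive SRTW, but it can work as a memory aid without being named in the item.
- *Some 35 to 40 failures are lost.* That figure counts people exposed to the gap, under assumptions. It does not count failures.
- *The planned 15-point difference shrinks to 13.5 or 12 points.* That follows from 15 × (sensitivity + specificity − 1) at assumed values of 0.95 or 0.90, and only if both arms return to work equally often. If return also differed by 15 points, adding (1 − specificity) × 15 gives 14.25 or 13.5. The protocol supports none of these inputs.
- *Listing T2 for the 12-month item is an error with consequences.* An on-time T2 cannot trigger that item, but a late T2 after an early return could. The branch is harmless.

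**Conclusion.** The point holds as a gap in the described data collection. On the natural reading of the relapse subsection, each participant back within about 12 months passes one survey with no relapse item, and the deciding answer comes 12 to 18 months after RTW. The loss is confined to returners who exceed the limit after the first item, complete the interim survey and then drop out. For them an already settled failure becomes a missing value, and the stated imputation has only baseline information with which to predict it.

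The size is uncertain and probably modest: about 35 to 40 of 506 exposed under the stated drop-out and return assumptions, with a minority of them lost failures at the planned rates. The direction of any bias in the arm comparison cannot be derived from the protocol. The conclusion rests on surveys being on time and on Table 2 not showing a repeat. Participants returning after month 12 never reach the 12-month item by T4; that is a related gap but a separate matter.

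**What to change.** In the subsection on relapse after RTW:

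- Route the existing first relapse item to every participant with a confirmed RTW at each survey until the 12-month item has been answered.
- Restrict it to absence within 12 months of the entered RTW date, and ask participants to answer from the absence list they already keep.
- Score SRTW as failed once any survey reports that the limit was exceeded within the window.
- Use the interim answers in the imputation model for those whose 12-month answer is missing.
- Keep the 12-month yes/no item as the deciding item for success, so that the endpoint definition does not change during the trial. Replacing it with absence-day counts now would mix two measurement methods within one endpoint, since recruitment began in September 2021.
- If Table 2 already repeats the item, align the text with it. The mention of T2 can stay.

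The cost is an amendment and one extra short item per follow-up survey. The item will be unavailable for surveys already completed, so those participants keep the present gap.
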